**LIST OF ABBREVIATIONS AND RELEVANT DEFINITIONS**

|                 |                                                                                                                    |
|-----------------|--------------------------------------------------------------------------------------------------------------------|
| 6-MP     | 6-mercaptopurine                                                                                            |
| γ-GT     | Gamma-Glutamyl Transferase                                                                                  |
| AD       | Atopic Dermatitis                                                                                           |
| AE       | Adverse Event                                                                                               |
| ALAT     | Alanine aminotransferase                                                                                    |
| ALP      | Alkaline phosphatase                                                                                        |
| ASAT     | Aspartate aminotransferase                                                                                  |
| AUC      | Area-Under-the-Curve                                                                                        |
| BCG      | Bacillus Calmette-Guérin                                                                                    |
| CCMO     | Central Committee on Research Involving Human Subjects; in Dutch: Centrale Commissie Mensgebonden Onderzoek |
| CI       | Confidence Interval                                                                                         |
| CK       | Creatine Kinase                                                                                             |
| CRF      | Case Report Form                                                                                            |
| CV       | Curriculum Vitae                                                                                            |
| DSMB     | Data Safety Monitoring Board                                                                                |
| EQ-5D-5L | EuroQol 5 dimensions 5 levels Health related Quality of Life questionnaire                                  |
| HRQoL    | Health Related Quality of Life                                                                              |
| FTU      | Finger-Tip-Unit                                                                                             |
| GCP      | Good Clinical Practice                                                                                      |
| GMP      | Good Manufacturing Practice                                                                                 |
| HECSI    | Hand Eczema Severity Index                                                                                  |
| IC       | Informed Consent                                                                                            |
| IGA      | Investigator Global Assessment                                                                              |
| LDL      | Low Density Lipoprotein                                                                                     |
| METC     | Medical research ethics committee (MREC); in Dutch: medisch ethische toetsing commissie (METC)              |
| PaGA     | Patient Global Assessment                                                                                   |
| PGA      | Physician Global Assessment                                                                                 |
| PROM     | Patient rated outcome measure                                                                               |
| QOLHEQ   | Quality of Life in Hand Eczema Questionnaire                                                                |
| RCT      | Randomized Controlled Trial                                                                                 |
| (S)AE    | (Serious) Adverse Event                                                                                     |

|                |                                                                                                                                                                                    |
|----------------|------------------------------------------------------------------------------------------------------------------------------------------------------------------------------------|
| SCORAD  | Severity Scoring of Atopic Dermatitis                                                                                                                                       |
| SPC     | Summary of Product Characteristics (in Dutch: officiële productinformatie IB1-tekst)                                                                                        |
| Sponsor | The sponsor is the party that commissions the organisation or performance of the research, in the case of this protocol embodied by the University Medical Center Groningen |
| SUSAR   | Suspected Unexpected Serious Adverse Reaction                                                                                                                               |
| T4      | Thyroxine                                                                                                                                                                   |
| TGN     | Thioguanine-nucleotide                                                                                                                                                      |
| TPMT    | Thiopurine methyltransferase                                                                                                                                                |
| TSH     | Thyreoid Stimulating Hormone                                                                                                                                                |
| UV      | Ultraviolet                                                                                                                                                                 |
| WMO     | Medical Research Involving Human Subjects Act (in Dutch: Wet Medisch-wetenschappelijk Onderzoek met Mensen)                                                                 |

## SUMMARY

**Rationale:** hand eczema is a common condition with a 1-year period prevalence up to 10%. Systemic treatment with alitretinoin is registered for all clinical types of hand eczema. However, it is especially effective in the hyperkeratotic subtype, and less effective in non-hyperkeratotic forms. Azathioprine is often prescribed for hand eczema in daily practice, and has a beneficial effect in non-hyperkeratotic subtypes. A few small studies support this observation. The efficacy of azathioprine in non-hyperkeratotic hand eczema could prove superior to that of alitretinoin.

**Objective:** to compare the efficacy of alitretinoin and azathioprine in the treatment of severe chronic non-hyperkeratotic hand eczema.

**Study design:** randomized prospective open-label trial with blinded outcome assessment, set in a university dermatology clinic, tertiary referral center. Assessment of severity and laboratory measurements in this study will be conducted corresponding to daily practice in our department.

**Study population:** adult patients (age 18-75 years) with severe chronic non-hyperkeratotic hand eczema, visiting the Department of Dermatology of the University Medical Center Groningen.

**Intervention:** group I: alitretinoin 30mg once daily. Group II: azathioprine 1.5 or 2.5mg/kg/day in 2 doses. The treatment period is 24 weeks.

**Main study parameters/endpoints:** the primary endpoint for efficacy is response to treatment, defined as an improvement of  $\geq 2$  steps on the Physician Global Assessment (PGA), developed by Ruzicka et al, after 24 weeks of treatment.

Secondary endpoints are improvement in: mean PGA at 12 and 24 weeks, the Hand Eczema Severity Index (HECSI) score, the Quality Of Life Hand Eczema Questionnaire (QOLHEQ), and a Patient Global Assessment (PaGA) of improvement. Adverse events will be registered, as well as time to response. Furthermore cost-utility, quality adjusted life years (QALYs) and cost-effectiveness will be assessed with the EQ-5D-5L questionnaire while monitoring treatment related costs.

**Nature and extent of the burden and risks associated with participation, benefit and group relatedness:** this trial is designed in a way that minimizes the burden and risks for the patient, because it will be carried out according to daily practice at our department. No additional laboratory measurements will be carried out next to measurements that are routinely assessed in treatment with one of both study drugs. One extra visit is needed to give patients consideration time before participation in the study. Results of the trial can be related to the population of patients with severe chronic non-hyperkeratotic hand eczema.

## 1. INTRODUCTION AND RATIONALE

Hand eczema is a common skin disease of the hands. It can have far-reaching personal, psychological and occupational consequences that may have a drastic impact on the life of those affected. A point prevalence of 4% and a 1-year-period prevalence up to 10% in the general population in Sweden have been reported. (1) A Danish study in young adults showed an incidence of 8.8 per 1000 person-years, a point prevalence of 7.1% and a 1-year-period prevalence of 14.3%. Women are significantly more often affected than men. (2)

The clinical presentation of hand eczema varies widely, ranging from erythematous fissured skin to a vesicular eruption or palmar hyperkeratosis. The disease could also be approached etiologically, considering exogenous factors causing contact allergy (e.g. nickel, perfumes) and irritant contact dermatitis (e.g. water, soap) in addition to endogenous factors like atopic dermatitis. (3)

There is general consensus concerning the first line treatment of hand eczema in various guidelines. Emollients and topical corticosteroids are considered to be the mainstay of treatment in mild forms. If these fail, secondary options like phototherapy and systemic treatment are available. (3-6) A recent Cochrane review (unpublished), however, states that conclusions on the best way to treat hand eczema cannot be drawn from the wide diversity of studies that were carried out up until now. More head-to-head trials are needed. (7)

Alitretinoin is the only registered systemic treatment option for all clinical types of severe chronic hand eczema in the Netherlands. It is currently the most investigated drug in terms of patient numbers in the second line treatment of severe chronic hand eczema. In well-designed, pharmaceutical sponsored trials, 30 mg alitretinoin a day resulted in a clear or almost clear response in 48% of the participants, compared to 17% in placebo. In the hyperkeratotic subtype 54% responded, compared to 12% in the placebo group. In two non-hyperkeratotic subgroups (defined as pompholyx and fingertip in the study) only 33% of participants reached clearance or almost clearance, compared to 12-30% in the placebo group. (8-10)

In the Netherlands, alitretinoin is registered since September 2013. It has never been compared to immunomodulating systemic drugs that are currently considered to be a second or third line alternative treatment for severe hand eczema. A trial comparing alitretinoin to cyclosporine ended prematurely due to the inability to include the total number of participants. (11)

In our clinical experience, supported by a retrospective assessment of patient data from our department (unpublished), azathioprine has beneficial effects on hand eczema. This concerns mainly the non-hyperkeratotic forms in which a response of 60% is estimated. A few small studies have shown that azathioprine may have a beneficial effect on hand

eczema. Scerri et al found a 75% good to excellent sustained clinical response in a case study in which pompholyx patients were treated with azathioprine. (12) In a case study by Pearce et al, 6 patients were treated with azathioprine for lymphoedema and hand dermatitis. 50% of patients reported a beneficial effect of the treatment. (13) In an Indian randomized comparative trial, conducted in 2013, chronic hand eczema patients were treated with either topical clobetasol propionate 0,05% cream alone, or in combination with azathioprine. A 91% improvement of hand eczema severity index (HECSI) score at 24 weeks was found in the azathioprine group, compared to 39% in the control group. (14)

In patients with atopic dermatitis (AD) who were treated with azathioprine a mean relative reduction in severity scoring of atopic dermatitis (SCORAD) was found in 39% of patients. Furthermore, an improvement to cleared, minimal or mild disease (investigator global assessment (IGA) <2) in 68.2% of all patients was found at 12 weeks. (15) Patients with AD frequently have involvement of the hands. (6) It is our clinical experience that these patients, when treated with systemic therapy, often show rapid healing of their hands as well.

Although these studies show favorable results, more studies on the use of azathioprine in the treatment of hand eczema are needed. This trial aims to compare alitretinoin to azathioprine in the treatment of severe chronic non-hyperkeratotic hand eczema. The study assesses the efficacy of both treatments and will show head-to-head results, which should contribute to uncovering the best treatment strategy for hand eczema.

## **2. OBJECTIVES**

Primary objective: to compare the efficacy of alitretinoine and azathioprine in the treatment of patients with severe chronic non-hyperkeratotic hand eczema.

Secondary objectives:

- to compare time to response
- to compare health related quality of life
- to compare improvement in severity of hand eczema, assessed by the patient
- to compare safety
- to compare cost-utility and cost-effectiveness

### 3. STUDY DESIGN

This study is designed as a randomized prospective open label study (or RCT). It will be conducted at the Department of Dermatology of the University Medical Center of Groningen, a tertiary referral center. Assessment of disease severity, laboratory measurements and quality of life in this study will be conducted comparable to daily practice assessments at our department.

The duration of the study for an individual patient is 24 weeks. The expected total duration of the study is 1.5 years.

Flow chart of study design:

[figure not shown]

## 4. STUDY POPULATION

### 4.1 Population (base)

The study population will exist of adult patients with severe chronic non-hyperkeratotic hand eczema, visiting the Department of Dermatology of the University Medical Center Groningen.

Non-hyperkeratotic hand eczema will be diagnosed following the criteria of the Danish Contact Dermatitis Group. (6) The severity of the hand eczema at the screening will be graded by means of a Physician Global Assessment using a validated Photoguide. (16)

Woman in the fertile age will be required to use proper contraception methods. Men and women of all ethnicities of 18 years and older will be recruited.

Patients meeting all inclusion criteria, while not meeting any of the exclusion criteria, will be asked to participate.

Our sample size calculation showed a total of 116 patients need to be included. Given the fact that 300-350 individual patients with hand eczema visit our outpatient eczema clinic every year, and the mean severity is high because our department is a tertiary referral center, we believe this number to be feasible.

### 4.2 Inclusion criteria

In order to be eligible to participate in this study, a subject must meet all of the following criteria:

- Age  $\geq 18$  years and  $\leq 75$  years
- Severe chronic non-hyperkeratotic hand eczema for a minimum duration of 3 months as defined by a Physician Global Assessment (PGA) using a validated Photoguide (16)
- Refractory to standard therapy, defined as:
  - Patients received treatment with topical corticosteroids of class II or higher for at least 8 weeks within 3 months before enrolment, with either no response or a transient response
  - Patients had also received standard skin care, including emollients and barrier protection as appropriate, without significant improvement
  - Patients had avoided irritants and allergens, if identified, without significant improvement

- Women of childbearing potential are required to use at least two forms of contraception for at least 1 month before starting treatment, during treatment, and for at least 1 month after finishing treatment; these women are required to take monthly pregnancy tests
- Able to provide written Informed Consent
- Able to speak and read the Dutch language

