## **6.6 Dosages, dosage modifications and method of administration**

The study drugs will be distributed to participants in amounts that allow drug intake as per protocol up to the next visit, 4 weeks later.

Dosage reduction is allowed in both groups in case of abnormal findings on physical examination, laboratory markers, and/or adverse events. Alitretinoin dose can be reduced from 30mg/day to 10mg/day, in accordance with the SPC-text.

*Alitretinoin* capsules need to be administered orally once daily, during a meal.

*Azathioprine* tablets need to be administered orally with a glass of liquid (200ml), during a meal.

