#### 8.1.2 Secondary study parameters/endpoints

##### *Severity of hand eczema*

- Between-group difference in mean change in PGA between baseline and 12 and 24 weeks.
- Between-group difference in response to treatment between baseline and 12 weeks of treatment.
- Between-group difference in mean change between baseline and week 4, 8, 12 and 24, assessed by the Hand Eczema Severity Index (HECSI) score. (21) The HECSI is an objective severity assessment based on clinical symptoms only. It includes erythema, fissures, vesicles, scaling, oedema, papules and measurement of the affected area. The score ranges from 0-360, with 360 indicating the most severe eczema.
- Between-group difference in time to response (time to first PGA improvement of  $\geq 2$  steps). This is only measured at control visits so possible outcome is limited to 4, 8, 12 and 24 weeks.

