## 8.3 Study procedures

Procedures part of standard medical treatment:

According to daily practice, a detailed patient history is obtained of all newly referred patients with hand eczema, and they are planned for patch testing to exclude contact allergy. During this first period, patients are treated with topical corticosteroids and emollients. Standard skin care advice is provided and exposure to provoking factors is discussed. If a relevant contact allergy is ruled out and the hand eczema proves to be refractory to topical therapy and/or UV therapy, the next step is systemic therapy. These patients are a candidate for the current study.

Laboratory analysis is performed to verify contra-indications for systemic treatment; in the current study alitretinoin or azathioprine. For azathioprine this check takes 4 weeks, due to the necessary measurement of TPMT (see paragraph 6.5). During therapy, standard

monitoring of blood values is carried out, according to SPC texts and current guidelines. At every visit, the Physician Global Assessment (PGA) for severity is determined (9) and the hand eczema is scored using the Hand Eczema Severity Index (HECSI, see appendix) (21), corresponding to our daily practice. Additionally, a Patient Global Assessment (PaGA) for improvement is obtained at week 12 and 24. Furthermore, health related quality of life is scored with a Dutch version of the Quality of Life in Hand Eczema Questionnaire (QOLHEQ, see appendix) at the start of therapy, at week 12 and week 24. (27)

Standard laboratory tests to be performed include:

*Alitretinoin*: at week 0, 4, 8, 12 and 24, laboratory tests are carried out, including: full blood count, ASAT, ALAT, ALP,  $\gamma$ -GT, serum creatinine, cholesterol, triglycerides, HDL, TSH, T4, glucose. At baseline, a pregnancy test will be carried out.

*Azathioprine*: at pre-baseline (week -4) TPMT activity will be measured, as described in paragraph 6.5. Furthermore, other laboratory tests are carried out, including: full blood count, ASAT, ALAT, ALP,  $\gamma$ -GT, bilirubine and serum creatinine. At week 1, 2, 4, 8, 12 and 24, these will be repeated.

Procedures extra for this study:

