#### *Azathioprine (from SPC text) (18)*

Azathioprine is well absorbed following oral administration. Peak plasma concentrations are reached 1-2 hours after taking a dose. Azathioprine is distributed rapidly throughout the body. The plasma half life is 3-5 hours. Only 30% of the medicinal product binds to plasma proteins. 12.5% enter the cerebrospinal fluid.

Azathioprine is extensively metabolised to 6-thioinosinic acid and methyl mercaptopurine-ribonucleotide, which, in part, are responsible for the effect of the medicinal product. The effect in-vivo is complicated by the action of methyl-nitroimidazole, which is also found.

Up to 50% of a dose is excreted in urine during the first 24 hours after administration, with approximately 10% as unchanged substance. Only 12.6% of the dose is excreted during 48 hours with the faeces. There is no evidence for enterohepatic circulation.

A lowered dosage for patients with reduced renal function may be necessary, probably as a result of reduced elimination of the active metabolites of azathioprine.

Also in patients with hepatic impairment the metabolism of azathioprine is altered.

Conversion into the active form is reduced, and especially the breakdown to eliminable metabolites is diminished.

Mercaptopurine, a metabolite of azathioprine, has been identified in the colostrum and breast-milk of women receiving azathioprine treatment.

g. Study population

In general, otherwise healthy subject with severe, chronic non-hyperkeratotic hand eczema will be included. Woman with child bearing potential will only be included in the study if they agree to use proper contraceptive methods during study period and up to two months following end of study.

h. Interaction with other products

For this section the reader is referred to paragraph 5.2 and the SPC text of alitretinoin and azathioprine. (10,18)

i. Predictability of effect

No biomarkers for effect have been determined.

j. Can effects be managed?

*Alitretinoin (from SPC text) (10)*

Alitretinoin is a derivative of vitamin A. Alitretinoin has been administered in oncological clinical studies at dosages of more than 10-times of the therapeutic dosage given for chronic hand eczema. The adverse effects observed were consistent with retinoid toxicity, and included severe headache, diarrhoea, facial flushing, hypertriglyceridemia. These effects were reversible.

It can be concluded that the (reversible) effects can be properly managed.

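### The monthly pregnancy tests required in section 4.2 are missing from section 8.3 and from both schedule tables, and the 4-week supply interval in section 6.6 does not fit the gap from week 12 to week 24

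*Protocol*

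**What the plan says.** **Pregnancy testing.** Protocol section 4.2 applies to women of childbearing potential without regard to arm. It asks for contraception before and during treatment and "for at least 1 month after finishing treatment; these women are required to take monthly pregnancy tests". In section 8.3 the alitretinoin paragraph adds one line: "At baseline, a pregnancy test will be carried out". The azathioprine paragraph lists TPMT activity and then "full blood count, ASAT, ALAT, ALP, $\gamma$ -GT, bilirubine and serum creatinine. At week 1, 2, 4, 8, 12 and 24, these will be repeated", with no pregnancy test at any time. Tables 1 and 2 have rows for laboratory control and adverse events but none for pregnancy testing.

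**Visits.** Section 8.1.2 says of time to response: "This is only measured at control visits so possible outcome is limited to 4, 8, 12 and 24 weeks". Both tables agree, apart from two extra laboratory-only contacts at weeks 1 and 2 for azathioprine.

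**Drug supply.** Section 6.6 has study drug handed out "in amounts that allow drug intake as per protocol up to the next visit, 4 weeks later".

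**Contraception after treatment.** Section 4.2 asks for two forms, continued for at least 1 month after treatment. Section 6.2 gives 1 month after alitretinoin. Section 13.1 g asks for proper "contraceptive methods during study period and up to two months following end of study".

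**The concern.** The protocol treats pregnancy as a serious matter. Section 5.2 calls it absolutely contraindicated on alitretinoin, section 6.4 lists azathioprine as possibly teratogenic, section 4.3 excludes pregnant women, and section 8.4.1 makes evidence of pregnancy a reason for withdrawal. Yet after baseline no procedure in section 8.3 would detect a pregnancy, and in the azathioprine arm none is named even before the first dose. Trial staff work from the procedures section and the schedule tables. A test that appears only among the inclusion criteria is easily missed, and the protocol names no route, responsible person or record for it.

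The supply sentence raises a smaller, separate question. It states an interval that does not exist for the second half of treatment, so the dispensing rule after week 12 is ambiguous.

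**Working it through.** **Inputs.** Visit weeks on treatment: 0, 4, 8, 12, 24 (section 8.3, Tables 1 and 2). Treatment length: 24 weeks (section 6.5 for alitretinoin; the Summary for both arms). Supply interval: 4 weeks (section 6.6). Test interval: monthly (section 4.2). One calendar month = 365.25 / 12 / 7 = 4.35 weeks.

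**1. The plan's own 4-week interval.** Visit intervals: 4 − 0 = 4; 8 − 4 = 4; 12 − 8 = 4; 24 − 12 = 12. The stated interval is reproduced for 3 of 4 and fails for the last. That last interval is 12 / 24 = half of treatment.

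**2. Can the visit windows close the gap?** Section 8.3 permits a deviation of up to 14 days from week 9. The shortest possible gap is (24 − 2) − (12 + 2) = 8 weeks and the longest is (24 + 2) − (12 − 2) = 16 weeks. Even the shortest is twice the stated 4 weeks.

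**3. Tests implied by the monthly rule.** Section 4.2 does not say whether monthly means every 4 weeks or every calendar month, so both are shown, counting one test at the start of treatment.
- Every 4 weeks: 0, 4, 8, 12, 16, 20, 24, which is 7 tests. Weeks 16 and 20 have no visit.
- Every 4.35 weeks: 0, 4.3, 8.7, 13.0, 17.4, 21.7, which is 6 tests. The next, at 26.1, falls after treatment. Three of the six (13.0, 17.4, 21.7) lie between weeks 12 and 24.

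Any tests in the months before or after treatment are left out, because section 4.2 does not say whether they are meant.

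**4. Tests named in the procedures.**

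| Source | Alitretinoin | Azathioprine |
|---|---|---|
| Implied by section 4.2 | 6 to 7 | 6 to 7 |
| Named in section 8.3 text | 1 | 0 |
| Row in Table 1 or 2 | none | none |
| Not named anywhere in the procedures | 5 to 6 | 6 to 7 |

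**5. Contraception windows (side note).** One month is about 4.3 weeks and two months about 8.7 weeks. The wording differs in three ways: length (at least 1 month, against up to two months), starting point (end of treatment, against end of study), and method (two forms, against proper methods). Section 12.5 defines end of study as the last patient's last visit, which for an individual woman can be much later than her own last dose.

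**The case against.** The case against starts from the fact that section 4.2 does not tie the tests to clinic visits. The laboratory lists in section 8.3 are not worded as exhaustive, that section also refers to product texts and guidelines for blood monitoring, and naming a baseline test does not exclude later ones. Tests could be done at home or through a pharmacy. This stands so far: the testing conflict is one of omission, and nothing in the protocol says monthly tests will not be done. It does not supply the missing route, and it does not explain why one arm has a baseline test and the other has none.

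Stronger readings are tempting, and the document does not support them.

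- **That supply stops at week 16, leaving 8 weeks uncovered and damaging the 24-week primary outcome.** The operative instruction in section 6.6 is supply up to the next visit, which after week 12 means week 24. The 4-week phrase is then a wrong description of the interval. The sentence is ambiguous, but an interruption of treatment is not shown.
- **That the supply sentence is a failed pregnancy safeguard.** No section links dispensing to pregnancy prevention.
- **That the contraception windows cannot both be met.** At least 1 month and up to two months overlap, and a woman who continues through the longer window satisfies both.
- **That the 1-month contraception lead-in is impossible because alitretinoin starts 1 week after screening.** A woman already using two forms at screening meets it, and the consideration week in section 8.2 is a minimum.
- **That written instructions to patients and sites will diverge.** The patient information is a separate document not at hand, and the trial has one centre.

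**Conclusion.** Two inconsistencies hold. First, a pregnancy-testing requirement that section 4.2 applies to both arms is not carried into section 8.3 or the tables: 1 test (alitretinoin) or 0 (azathioprine) is named against 6 to 7 implied, and there is no visit in the 12 weeks in which 2 or 3 of them fall due. Second, the 4-week interval in section 6.6 is wrong for weeks 12 to 24, half the treatment period, and leaves the supply rule unclear there. The contraception wording is a side note on consistency.

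The counts assume a full 24 weeks on treatment, one test at the start, and monthly read as either 4 weeks or a calendar month. The finding that the procedures name fewer tests than section 4.2 requires does not depend on which is chosen. A reader might infer that the safeguards as a whole cannot be operated as written. That goes too far, since the requirements can be met together; the fault is that the schedule does not lead staff to meet them. Sample size and analysis are unaffected.

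**What to change.** - Reconcile section 4.2 with section 8.3 and Tables 1 and 2, so that a single pregnancy-testing rule appears in the procedures for each arm and as a row in each table. State how it is met between weeks 12 and 24, who is responsible and where the result is recorded.
- Reconcile the supply sentence in section 6.6 with the visit schedule, so that dispensing after week 12 has one reading.
- Harmonise the contraception wording in sections 4.2, 6.2 and 13.1 g: length, starting point and number of methods.

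Which frequency, supply rule and contraception window hold is for the responsible clinicians and the ethics committee. The cost is protocol wording and one row in each table. If the monthly rule is kept, there is also the cost of the tests themselves and of some contacts between weeks 12 and 24.
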